## Abstract

**Background:**

Familial cerebral cavernous malformations (fCCMs) are a rare genetic autosomal dominant cerebrovascular disease characterized by multiple cerebral and spinal angiomas. The condition is caused by mutations in KRIT1 (CCM1), CCM2 (malcavernin), or PDCD10 (CCM3) and may lead to intracerebral hemorrhage (ICH) or non-hemorrhagic focal neurological deficits (FNDs), potentially leading to severe disability and even death. To date, little is known about disease progression, and tools to identify patients at higher risk are lacking.

**Methods:**

Pediatric and adult fCCM patients, whether symptomatic or asymptomatic, will be enrolled and followed annually over a 2-year period. Participants will undergo clinical assessments, blood sampling, and 3 T brain MRI scans at baseline, 12 months, and 24 months. The primary outcome is the new occurrence of symptomatic ICH or FNDs attributable to CCMs over 24 months. Patient characteristics will be assessed for the primary and secondary endpoints and illustrated using Kaplan–Meier curves and Cox proportional hazard regressions. This trial is registered with ClinicalTrials.gov, NCT06983132 and is currently recruiting participants.

**Discussion/conclusion:**

Despite increasing efforts in basic and clinical research and an improved understanding of the pathogenic mechanisms underlying fCCM, tools to predict disease progression, identify at-risk individuals, and pinpoint effective therapeutic targets are still lacking. This study aims to create the largest Italian cohort of fCCM patients, who will be monitored closely over time to collect data that may help identify risk factors and disease trajectories. The collection of standardized information on clinical and radiological evolution, along with results from circulating biomarkers, will help address the complexities of the disease and may suggest potential reliable markers of disease progression.

**Clinical trial registration:**

ClinicalTrials.gov, identifier NCT06983132.

## Introduction

1

Familial cerebral cavernous malformations (fCCMs) are a rare genetic autosomal dominant cerebrovascular disease characterized by microvessel dilatations with deficient blood–brain barriers and disrupted inter-endothelial junctions, resulting in vessel hyperpermeability and fragility. CCMs may result in intracerebral hemorrhage (ICH) or non-hemorrhagic focal neurological deficits (FNDs) due to the growth of lesions in eloquent brain areas, potentially leading to severe disability and even death. Additionally, the disease may cause seizures and recurrent headaches. Familial CCMs (fCCMs) are a rare condition caused by loss-of-function mutations in one of three independent genes: KRIT1 (CCM1), malcavernin (CCM2), or programmed cell death 10 (PDCD10/CCM3). To date, no curative treatment exists, and little is known about clinical, radiological, or blood biomarkers that can monitor disease progression or identify patients at higher risk of serious clinical events.

Despite improved understanding of its pathophysiology, reliable biomarkers to monitor progression and stratify risk are still lacking. This underscores the need for longitudinal studies integrating clinical, imaging, and biomarker data.

Brain MRI is a valid tool to diagnose and monitor CCM lesions, but it is expensive and may be poorly tolerated by some patients. Circulating biomarkers could complement imaging as a tool for patient classification and monitoring disease progression.

Based on our group’s previous experience in the context of the Treat_CCM phase 2 clinical trial (1, 2) and a review of the literature, we identified a set of biochemical parameters that may predict CCM progression, offering insights into the underlying biological mechanisms and potential therapeutic approaches for this rare condition.

## Methods and analysis

2

### Study design

2.1

CCM_Italia is a multicenter, non-profit, prospective, observational, non-pharmacological study. Pediatric and adult patients with genetically confirmed fCCMs will be enrolled according to the inclusion and exclusion criteria designed to include a large representative cohort reflecting the heterogeneity of fCCM, ranging from asymptomatic to high-risk cases. CCM_Italia aims to identify clinical, imaging, and biochemical predictors of disease progression.

Patients will be enrolled during the clinical visits planned with their treating physician. As a non-interventional registry, participation will not influence routine clinical care or surgical decisions. Patients’ enrollment will take place after successful screening and confirmation of eligibility at Fondazione IRCCS Cà Granda Ospedale Maggiore Policlinico (Policlinico Milano) in Milan, Azienda Ospedaliero-Universitaria Policlinico in Bari, Azienda Ospedaliero Universitaria San Giovanni e Ruggi d’Aragona in Salerno, and Azienda Ospedaliero Universitaria Careggi in Firenze. Pediatric patients’ enrollment will take place primarily at IRCCS Pediatrico Istituto Giannina Gaslini in Genova.

The study will combine longitudinal clinical data with MRI as well as peripheral blood collection at baseline (T0) and after 1 (T1) and 2 (T2) years to identify circulating biomarkers for assessing clinical evolution and the incidence of adverse CCM-related clinical events in these patients. MRI will be performed according to a standardized protocol, and the obtained images will be assessed centrally by expert radiologists at Fondazione IRCCS Cà Granda Ospedale Maggiore Policlinico. Biological samples will be stored long-term in the UN EN ISO 9001:2015-certified “SATURNE” biobank at Istituto di Ricerche Farmacologiche Mario Negri IRCCS.

#### Inclusion criteria

2.1.1

Patients who simultaneously meet the following criteria will be included:

Adult and pediatric patients with familial cerebral cavernous malformations documented by multiple CCM lesions on MRI and a confirmed pathogenic mutation in CCM1, CCM2, or CCM3;Symptomatic or asymptomatic;Life expectancy at least as long as the study follow-up duration;Written informed consent provided by the patient (or caregivers in the case of minors) to participate in the study.

#### Exclusion criteria

2.1.2

The patient who does not meet the inclusion criteria mentioned above or meet any of the following conditions will not be eligible to participate in the study:

Implanted pacemaker or any other condition preventing MRI;Inability to cooperate with the study procedures.

#### Exit study criteria

2.1.3

A patient will be considered discontinued from the study only if they withdraw consent for follow-up at the participating center or are lost to follow-up after all means of contact have been exhausted. Surgical correction of angiomas during follow-up will not necessitate discontinuation from the study. In cases of discontinuation, the status of the patient at the last visit or last available contact will be used for the final analysis. Vital status may be ascertained through public records if all other means of contact fail.

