#### Sample size calculation

2.3.5

The primary endpoint, the new occurrence of CCM-related clinical events, defined as ICH and FNDs, excluding seizures, is expected in approximately 5.6% of the population based on the Treat_CCM trial (1). Assuming that 5.6% of subjects in the CCM_Italia cohort will develop a CCM-related clinical event, at least 100 patients (including a dropout of 8%) are needed to estimate this proportion with 95% confidence and 4.7% absolute precision.

According to the Treat_CCM study, 55% of fCCM patients are expected to experience increased disease activity. Dividing the population by the median level of a biomarker or imaging marker of interest (resulting in 2 groups of 50 individuals) would provide us a statistically significant result if the HR of this biomarker is at least 2.15 (power 80%, *α* = 0.05) (6, 7).

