#### Statistical analysis

2.3.6

Baseline characteristics will be presented for the total population and by relevant variables (e.g., sex, age categories, and number of CCM lesions). Relevant patient subgroups, such as gene mutation, age groups, and presence of baseline symptoms, will be compared by descriptive univariate statistics. Prior experience of the consortium has shown that data are quite complete, and imputation for missing values was not performed.

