##### Primary endpoint

2.3.6.1

Patient characteristics will be compared using descriptive analyses to compare patients who reach the primary endpoint—the new occurrence of CCM-related clinical events, defined as ICH and FNDs, excluding seizures—to those who do not. The Kaplan–Meier curves will be constructed to assess the onset of the primary endpoint over time.

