##### Secondary endpoint

2.3.6.2

*Clinical endpoints*: individual components of the primary endpoint, the incidence of either ICH or FNDs, and other clinical secondary endpoints such as seizures, headache, or any hospitalization, will be assessed by means of descriptive analyses. In addition, the Kaplan–Meier curves will be constructed to illustrate the occurrence of clinical events over time.

*Disease activity*: In order to explore the discriminatory power of biomarkers, we will assess a secondary endpoint: disease activity. This will be defined as CCM-related adverse events or the development of at least 5 new CCM lesions during the 2 years of observation. Based on (2), we expect at least 55% of the participating fCCM patients to be classified as “active.” Patients will be divided by the median level of a biomarker or imaging marker of interest. Logistic regression analyses will be performed to identify circulating biomarkers independently associated with increased disease activity. All outcomes will be reported with 95% confidence intervals, and in the case of -omics assessments, corrections for multiple testing will be applied.

*Questionnaires*: Global cognitive function, depression, anxiety, and health-related quality of life will be assessed in adult patients at multiple time points, and any changes over time will be described and assessed using repeated measures ANOVA.

*Neuroimaging*: Different vascular lesion characteristics, as measured by MR imaging, will be assessed for the total population and by relevant characteristics:

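### The last-status rule for leavers is not limited to time-to-event outcomes, so the disease-activity logistic regression can count incompletely observed patients as 2-year negatives

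*Protocol article*

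**What the plan says.** Section 2.1.3 (Exit study criteria) of the protocol article allows discontinuation only for withdrawn consent or loss to follow-up. For those patients, "the status of the patient at the last visit or last available contact will be used for the final analysis". The sentence names no outcome and no method, so it covers every final analysis.

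Section 2.3.6.2 (Secondary endpoint) defines disease activity as a CCM-related adverse event or at least 5 new lesions over the 2 years of observation. The analysis is fixed: "Logistic regression analyses will be performed to identify circulating biomarkers independently associated with increased disease activity".

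For the primary endpoint, section 2.3.6.1 plans Kaplan-Meier curves and a descriptive comparison: "Patient characteristics will be compared using descriptive analyses to compare patients who reach the primary endpoint" with those who do not. The abstract also names Cox regression for primary and secondary endpoints.

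On missing data, section 2.3.6 says: "Prior experience of the consortium has shown that data are quite complete, and imputation for missing values was not performed".

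Section 2.3.5 (Sample size calculation) allows for 8% dropout and assumes that "55% of fCCM patients are expected to experience increased disease activity".

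**The concern.** A logistic model needs a known 2-year status for every patient it includes. A patient who leaves after baseline has no follow-up MRI, so no new lesion could be counted. A patient who leaves after the 12-month visit has been imaged for half of the window. A last contact need not include an MRI at all. If such a patient has had no event and fewer than 5 new lesions, the last status is not active, and the unqualified rule enters that as the 2-year result.

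The error runs one way: some truly active patients are recorded as inactive, and none the reverse. If dropout is unrelated to the marker, the marker's odds ratio is attenuated. If dropout is related to the marker, the odds ratio can be pushed either way, and an association can appear where none exists. This is the model planned for the circulating biomarkers, and section 2.1 gives the identification of predictors of progression as the study's aim.

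**Working it through.** **Inputs from section 2.3.5:** N = 100, 8% dropout, primary event proportion 5.6%, precision 4.7 points, active proportion 55%, two marker groups of 50, hazard ratio 2.15, power 80%, α = 0.05 (taken as two-sided).

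**The plan's own figures reproduce.**
- Precision: 1.96² × 0.056 × 0.944 / 0.047² = 91.9, so 92 patients; 92 / 0.92 = 100.
- Marker: the Schoenfeld formula, 4 × (1.96 + 0.842)² / (ln 2.15)², gives 54 events. The plan expects 0.55 × 100 = 55, which gives 81% power.

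**Assumption not in the document.** Let f be the share of the 24-month risk (cumulative hazard) observed before a leaver exits. With true proportion q, a leaver is seen to be active with probability 1 − (1 − q)^f. The proportion recorded under the literal rule is

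0.92 × q + 0.08 × [1 − (1 − q)^f].

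| Outcome | True | f = 0 | f = 0.5 | f = 1 |
|---|---|---|---|---|
| Disease activity | 55% | 50.6% | 53.2% | 55% |
| Primary event | 5.6% | 5.15% | 5.38% | 5.6% |

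Example for activity at f = 0.5: 1 − 0.45^0.5 = 0.329, and 0.92 × 0.55 + 0.08 × 0.329 = 0.532. Among 100 patients, the active ones recorded as inactive number 8 × 0.55 = 4.4 at f = 0 and 8 × (0.55 − 0.329) = 1.8 at f = 0.5. For the primary endpoint the most that can be missed is 8 × 0.056 = 0.45 events, or 0.45 percentage points.

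**Marker odds ratio.** Choose active proportions p_low and p_high that average 55% and satisfy 1 − p_high = (1 − p_low)^2.15. This gives 41.5% and 68.5%, and a true OR of 3.06. Apply the same formula within each marker half:

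| Dropout, low / high half | OR at f = 0 | OR at f = 0.5 |
|---|---|---|
| 8% / 8% | 2.75 | 2.96 |
| 4% / 12% | 2.29 | 2.75 |
| 0% / 16% | 1.91 | 2.56 |
| 12% / 4% | 3.33 | 3.19 |
| 16% / 0% | 4.05 | 3.45 |

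These use unrounded proportions. Starting from 0.415 and 0.685 exactly, the first row at f = 0 reads 3.07 shrinking to 2.76.

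**No true effect (55% active in both halves).** With 16% dropout in one half and none in the other, at f = 0 the OR is (0.462/0.538) / (0.55/0.45) = 0.70. At f = 0.5 the recorded proportion is 0.84 × 0.55 + 0.16 × 0.329 = 0.515, and the OR is 0.87. With 12% against 4%, the ORs are 0.84 and 0.93.

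**The case against.** The strongest reply is that section 2.1.3 does not say leavers are coded as inactive at 24 months. Status at last contact is the normal input for censoring, and methods that censor are planned: Kaplan-Meier, Cox in the abstract, and a hazard ratio behind the marker calculation. The inflation from 92 to 100 treats leavers as not evaluable for the primary proportion. The disease-activity analysis is secondary and exploratory, and an analysis plan that is not shown may settle the matter. The f = 0 figures are a bound, and nothing in the protocol supports putting all dropout in one marker half. With 50 per group, the standard error of a null log odds ratio is about 0.40, so its 95% interval spans a factor of about 2.2 each way, wider than any of these null biases.

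Much of this stands, and it rules out several stronger readings that a reader might infer:

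- **That all early leavers become negatives.** A patient with an event or 5 new lesions before exit keeps that status.
- **That the time-to-event analyses are wrong.** They are sound if censoring is non-informative.
- **That the primary endpoint is distorted.** A shift of at most 0.45 points is small beside 4.7-point precision, and the reached/not-reached comparison is descriptive with Kaplan-Meier beside it.
- **That section 2.3.6 is contradicted.** Its remark that "data are quite complete, and imputation for missing values was not performed" is in the past tense and rests on prior experience. It conflicts only if last status is carried to 24 months, and even then it is a tension, not a clear contradiction.

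The reply does not remove the central point. The protocol states a rule for the final analysis without limit and also fixes logistic regression for a 2-year outcome. The marker calculation keeps both groups at 50 with no dropout removed, so it does not show that leavers are excluded there. A later plan would have to narrow the protocol's sentence, not just add detail.

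**Conclusion.** The concern holds for the disease-activity logistic regression. Followed literally, the rule counts unobserved time as inactive for patients who leave before becoming active. At 8% dropout unrelated to the marker the effect is modest: recorded activity of 50.6% to 53.2% in place of 55%, and an OR of 2.75 to 2.96 in place of 3.06. If dropout depends on the marker, the bias can go either way; the extreme splits give 1.91 to 4.05. The documents neither show nor exclude such dependence, although a cohort that mixes asymptomatic and symptomatic patients makes dropout related to severity plausible.

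These sizes rest on the plan's 8% and 55%, on marker proportions derived from HR 2.15, and on the assumed f. They vanish as f approaches 1. Severity is moderate: a secondary analysis is affected, the primary endpoint barely so, and the remedy is cheap.

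**What to change.** 1. In section 2.1.3, replace the general sentence with one limited to time-to-event outcomes, which are censored at last contact.
2. In section 2.3.6.2, analyse disease activity with a discrete-time complementary log-log model over 0–12 and 12–24 months. Each patient contributes only intervals in which the outcome was assessed, up to the first in which the patient is active, with new lesions counted cumulatively from baseline. No unobserved interval then counts as inactive. The coefficient is a log hazard ratio under proportional hazards, which matches the hazard ratio used in section 2.3.5.
3. State when an interval counts as assessed, in particular when a clinical event occurs but the closing MRI is missing. Patients already active at exit should keep that status.

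Inverse-probability weighting of completers is not needed, and weights estimated from about 8 dropouts would be unstable.

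The change needs no new data. It costs a revised sentence, a short model specification and slightly more analysis work. A few patients contribute partial information in place of an assumed negative.

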### Study procedures

2.2

#### Patient enrollment and data collection procedures

2.2.1

Patients with successful screening (presence of inclusion criteria and absence of exclusion criteria) will be asked to sign informed consent. Each participant, at the time of enrollment, will be assigned a unique code so that only local investigators can trace the identity of enrolled subjects.

All patients who are included in the CCM_Italia cohort will undergo an annual clinical assessment according to clinical practice (T0-T1-T2). This assessment will be performed in the outpatient clinic at the referral hospital. During these routine follow-up patient visits, information will be collected on the following events: ICH, FNDs, seizures, recurrent headaches, hospitalizations, and death.

In accordance with clinical practice, an annual brain MRI will be performed in the Neuroradiology Unit of the referral hospital, preferably on the same day as the clinical assessment. If this is not possible, the MRI will be scheduled within 1 month for the inclusion visit T0 and within ± 40 days for follow-up visits (T1-T2). The MRI protocol will include sagittal 3D T1-weighted turbo field echo, sagittal 3D T2-weighted turbo spin echo, sagittal 3D fluid-attenuated inversion recovery, axial diffusion-weighted imaging, axial susceptibility-weighted imaging, axial T2-weighted gradient echo, and optional diffusion tensor imaging and axial spoiled 3D multi-echo gradient-echo sequences (SGRE) for quantitative susceptibility mapping (QSM). The current protocol is in line with standard clinical practice. The collected MRIs will be centrally assessed at the MRI core laboratory of IRCCS Fondazione Ca′ Granda Ospedale Maggiore Policlinico by blinded personnel. The following MRI variables will be recorded at baseline and follow-up examinations: CCM lesion characteristics including number, signal (8), size, and location of CCMs and size modifications, signs of *de novo* bleeding, and number of *de novo* lesions at 12 and 24 months. Image examples of each Zabramski type of lesion will be provided to ensure that raters understand the Zabramski classification system. A standardized interpretation of MR imaging features on T1, T2, and SWI images that are relevant to classification will be discussed. Raters will independently classify a set of 15 MRI cases and then review any discrepancies. Interrater reliability will be assessed using a separate set of 30 MRI cases, which raters will classify independently while remaining blinded to each other’s assessments. Cohen’s kappa will be calculated.

Advanced MRI techniques such as diffusion tensor imaging (DTI) and QSM, which are not routinely performed in the follow-up of CCM patients, will be applied if available at the center and analyzed at IRCCS Fondazione Ca′ Granda Ospedale Maggiore Policlinico in the MRI core laboratory to assess iron deposition (3) and structural integrity. DTI and QSM do not require contrast media injection. This analysis does not impose any extra burden on patients, as they already undergo an annual MRI as part of clinical practice.

In addition to the standard annual clinical assessment described above, adult patients will be asked to complete specific questionnaires for patient-reported outcome measures (PROMs) and patient-reported experience measures (PREMs) on an annual basis. These include the following standardized questionnaires: the Beck Depression Inventory-II (BDI-II) for depression; the State–Trait Anxiety and Quality of Life for anxiety; and Short Form 36 (SF-36) for quality of life, divided into the physical and mental component scales (PCS and MCS). Furthermore, cognitive function and disability will be assessed using specific questions in the questionnaire, which will be completed by the patient during the clinical visit; this usually takes 10–15 min (4). For minors, these questionnaires will not be applicable unless they have been specifically validated for their age category.

All patients’ clinical and radiological data, as well as outcomes of questionnaires and specific information on clinical events, will be de-identified and recorded in electronic case report files on the REDCap platform.

#### Biological sample collection and analysis

2.2.2

In addition to the standard annual clinical assessment, patients will undergo blood sample collection at the same time as their annual clinical visit. Three vials, containing a total of 15 mL of blood, will be collected at the outpatient clinic of the referral hospital during clinical visits at baseline (T0), 12 months (T1), and 24 months (T2) to obtain whole blood, EDTA plasma, and citrate plasma samples. Blood samples will be drawn from a peripheral vein into vacuum tubes containing sodium citrate and EDTA-K3 anticoagulants. The tubes will then be gently inverted 5–6 times and placed upright at room temperature. One aliquot of whole blood (1 mL) will be transferred into a cryovial. After collection, blood samples will be centrifuged within 2 h at 4 °C for 15 min at 2,000 × *g*. Plasma will then be aliquoted and stored locally at −70 °C before being periodically shipped on dry ice with a dedicated courier to the certified ISO 9001:2015 SATURNE biobank at the Mario Negri Institute for Pharmacological Research in Milan, Italy, where they will be centralized and stored long-term in a − 70 °C freezer under controlled conditions for further analysis. Standard operating procedures for sample collection, processing, and storage, as well as the necessary materials for blood collection, will be shared with all clinical centers participating in the study. All samples will be de-identified with a unique 6-digit code. All assays will be conducted according to the manufacturer’s instructions.

